### Objectives and hypotheses

Because of the paucity of studies on the effectiveness of psychological interventions for emotional problems in DM patients, especially regarding mindfulness based interventions, the purpose of this study is to test the effectiveness of a mindfulness-based psychological intervention. The primary outcome is emotional distress (symptoms of depression, anxiety, diabetes-specific stress, and general perceived stress). Secondary outcomes are quality of life, (diabetes-specific) mindfulness, and self-esteem, and our tertiary outcomes are self-management, glycemic control, and blood pressure. Finally, we will examine which patient characteristics (like the extent of complications and personality) predict which patients most likely benefit from the intervention.

With regard to our first outcome measure, we hypothesize that after an eight-week mindfulness-based training DM patients will experience significant greater reductions in emotional distress (diabetes-specific stress, anxiety, and depressive symptoms) compared to a wait-list control group. Concerning our secondary outcome measures, we hypothesize that the intervention will lead to greater improvements in psychological quality of life, dispositional (diabetes-specific) mindfulness, and self-esteem compared to a wait-list control group. In addition, we expect, consistent with two other studies [32,33], that changes in dispositional mindfulness will mediate the hypothesized effects of the intervention on above mentioned outcomes. Regarding our tertiary, more clinical, outcome measures, we hypothesize that the intervention will lead to better diabetes self-care, lower HbA_1c_, and lower BP in people with elevated BP. Finally, we are interested in personality and clinical factors that could possibly act as effect modifiers. We do not have clear expectations about the direction of the possible influence of these characteristics, being complications (yes/no), diabetes type (DM1 versus DM2), co-morbidity (yes/no), and personality.

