#### 1. Additional outcome measures

##### Personality

To measure personality dimensions we will use the subscale Extraversion (EPQ-E) of the shortened revised Eysenck Personality Questionnaire (EPQ-RSS) and the DS-14 to measure Type D personality. Persons with a Type D personality tend to experience high levels of emotional distress, but do generally not express these emotions. For the EPQ-E, the subscale Extraversion reflects sociability, assertiveness, and the tendency to experience positive emotions. The subscale consists of 12 dichotomous (yes/no) items [56]. The Committee on Test Affairs Netherlands rates the EPQ to be a reliable measure [57].

The 14-item Type D scale (DS14) measures both negative affectivity (NA) (e.g. "I often feel unhappy"; 7 items) and social inhibition (SI) (e.g. "I am a closed kind of person"; 7 items) [58]. Items are answered on a five-point Likert scale ranging from 'false' to 'true' *(0-4)*, with the score range for the NA and SI subscales being 0 to 28 [58]. We will use the standardized cut-off ≥ 10 on both subscales to identify Type D caseness [58,59]. The DS14 has been shown to be a valid and reliable instrument, with Cronbach's α of 0.88 and 0.86 and a 3-month test-retest reliability of r = 0.72 and 0.82 for the NA and SI subscales, respectively [58]. Furthermore, a recent study showed that Type D personality is a stable construct over an 18-month period and is not confounded by disease severity and measures of anxiety and depression [60,61]. Results from a study by Denollet et al [62] suggest that particularly the interaction between NA and SI is predictive of adverse health outcomes, more than the single traits [62].

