#### Planned analyses

Repeated measures analysis of variance ((M)ANCOVA) will be used to test the hypotheses concerning the differences between groups on the dependent variables over time. In these tests age, sex, and co-morbidity will be included as covariates, in addition to those other potentially confounding variables that will show an at least marginally significant (p < .10) difference between groups. The analyses concerning the subgroup effects will be conducted on the sample as a whole, whereby possible moderating variables, like complications and personality will be included in the analyses as between-subjects factors. All analyses will be based on the intention-to-treat approach.

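### Personality moderators are planned only as groups: if moderation is linear in the scores, a two-group cut loses about 36% to 51% of the information, so continuous-score models should be added beside the Type D factor

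*Protocol article*

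**What the plan says.** The Objectives section of the protocol article lists the effect modifiers as "complications (yes/no), diabetes type (DM1 versus DM2), co-morbidity (yes/no), and personality". It adds "We do not have clear expectations about the direction of the possible influence of these characteristics", so the question is exploratory.

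Planned analyses gives the model: "possible moderating variables, like complications and personality will be included in the analyses as between-subjects factors". The same paragraph says "In these tests age, sex, and co-morbidity will be included as covariates". Age, a continuous variable, is therefore a covariate, and a between-subjects factor in that paragraph is most naturally read as a grouping variable.

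The Personality section describes two instruments:

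- **DS14.** Two numeric subscales, "with the score range for the NA and SI subscales being 0 to 28". The grouping is fixed: "We will use the standardized cut-off ≥ 10 on both subscales to identify Type D caseness". The section closes by citing a study suggesting that "particularly the interaction between NA and SI is predictive of adverse health outcomes, more than the single traits".
- **EPQ-E (extraversion).** "The subscale consists of 12 dichotomous (yes/no) items". No cut-off is given.

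**The concern.** Two 21-plus-point scores become one yes/no variable before they enter the moderator analysis. Three things follow.

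- Patients just either side of 10 on a subscale are treated as different, while patients far apart on the same side are treated as alike. If the treatment effect changes gradually with the score, that discards information from interaction tests, which already have little power.
- One caseness term cannot show whether a modified effect comes from NA, from SI or from their product.
- Extraversion, if it is to be a factor at all, needs a grouping that the article does not give.

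At stake is how a null personality result is read. The Discussion presents the moderator analysis as a strength that may help allocate patients to treatments. A null Type D result could mean that personality does not modify the effect, or only that the coding was too coarse to show it.

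**Working it through.** **Inputs from the article.** N = 160 (80 per arm), alpha 0.05, power 0.80, a medium effect, an unstated attrition rate, and sizing for subgroup analyses with two equal groups (Sample size and power calculation). NA and SI run 0 to 28; caseness is 10 or more on both.

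**Assumptions, not in the article.** Normal scores, moderation linear in the score, a two-sided test, and the share of patients above the cut. The article gives no score distribution and no Type D prevalence, so a range is shown.

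**The plan's own figure.** Taking medium as d = 0.5, two-sided alpha 0.05 and power 0.80 give 63 per arm (64 by the t-test). An assumed 20% attrition raises 64 to 64/0.8 = 80 per arm, or 160. The stated total is thus consistent with 20% attrition but cannot be strictly reproduced. It neither supports nor weakens the present point.

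**Information kept by a cut.** With a share p above the cut, z the matching normal quantile and phi the normal density, the efficiency relative to the continuous score is E = phi(z)^2 / [p(1 - p)]. If the continuous interaction test has 80% power, power after the cut is Phi(2.80 x sqrt(E) - 1.96), because 1.96 + 0.84 = 2.80.

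| Share above cut | E | Information lost | Effective N (160 x E) | Power (80% if continuous) |
|---|---|---|---|---|
| 50% | 0.1592/0.25 = 0.637 | 36% | 102 | 61% |
| 30% | 0.1209/0.21 = 0.576 | 42% | 92 | 57% |
| 25% | 0.1010/0.1875 = 0.539 | 46% | 86 | 54% |
| 20% | 0.0784/0.16 = 0.490 | 51% | 78 | 50% |

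**The joint cut.** Type D requires both subscales to be high. The squared correlation of such an indicator with NA + SI was simulated for NA-SI correlations of 0.3 to 0.5 and prevalences of about 20% to 55%. It was 0.43 to 0.57, a loss of about 43% to 57%. The single-score table is therefore not an exaggeration for a moderator driven by the sum.

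**What the truth has to look like.** The two codings were compared by simulation (N = 160, NA-SI correlation 0.4, cuts at the mean, 3,000 runs). The continuous test has 3 degrees of freedom (arm by NA, SI and NA x SI); the planned test is arm by caseness.

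| True moderator | Power, continuous | Power, Type D yes/no |
|---|---|---|
| NA x SI product only | 0.59 | 0.12 |
| NA + SI | 0.63 | 0.50 |
| Type D caseness, 0.95 SD | 0.41 | 0.79 |

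The absolute powers depend on the chosen effect sizes; only the comparison within a row is informative. The first row is an extreme case. A pure centred product gives patients low on both traits the same modified effect as patients high on both, which a high/high indicator is poorly placed to detect. Cuts at the mean are also not the protocol's cut of 10.

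**The case against.** The strongest case for the plan is that Type D is an established joint construct with a standard cut-off fixed in advance. It is not a data-driven split, and it fits the two-group subgroup design used for sizing. If caseness itself moderates the effect, the planned term clearly beats the continuous test (0.79 against 0.41). Replacing it would then cost a great deal of power. This stands, and it is why the Type D factor should stay.

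Three stronger readings are tempting, and the article does not support them:

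- A reader might infer that a third to a half of the information is lost for the whole effect-modification question. Complications, diabetes type and co-morbidity are already categorical and lose nothing. Even for personality, the figure rests on assumed normality and linearity.
- A reader might take the sentence on NA and SI as the protocol's own statement that their interaction drives response to training. It reports what a cited study suggests about adverse health outcomes. That is prognosis, not treatment response.
- A reader might conclude that extraversion will be split at a cut chosen from the data. The article states no cut and does not say how extraversion is coded. Its grouping is only implied by the word for factors, and a fuller plan may settle it.

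The objection does not remove the core. Grouping is the stated approach for personality, the Type D cut is explicit, and the article holds no directional expectation that would justify relying on the category alone.

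**Conclusion.** The point holds in a limited form. For the personality modifiers only, with normal scores and linear moderation, a two-group cut loses about 36% (50/50) to 51% (20/80) of the information, and 80% interaction power falls to about 61% to 50%. Separately from power, one caseness factor cannot distinguish NA, SI and their product. If moderation truly follows the Type D category, the loss is nil and the planned coding is the better test. The documents cannot say which case applies, so relying on one coding is the weakness, not the use of Type D as such. Severity is minor: the analysis is exploratory and no main treatment comparison is affected.

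**What to change.** In Planned analyses, add to the moderator analyses a pre-specified model with baseline NA, SI and NA x SI as centred continuous scores, each with its interaction with arm. Enter extraversion as a continuous score with its arm interaction, which removes the need for a cut-off. Keep the pre-specified Type D caseness factor beside this as a reported analysis, not only a descriptive display. Keep factor coding for complications, diabetes type and co-morbidity.

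No new data are needed: Table 1 already collects the DS14 and EPQ-E at baseline. The cost is one more exploratory model to report, with results given as slopes instead of a difference between two named groups.

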### Ethical principles

The study protocol has been approved by the medical ethical committee of the St. Elisabeth Hospital in Tilburg, The Netherlands (P0948).

## Discussion

The present article provides an outline of the background and design of the Diabetes and Mindfulness (DiaMind) study. This study's objective is to test an intervention based on mindfulness training supplemented with elements from cognitive therapy that aims to improve emotional well-being of distressed patients with diabetes. For this purpose, an intervention group will be compared with a wait-list control group with treatment as usual.

Research on psychological interventions that aim to reduce emotional problems in DM patients is important, as emotional problems are associated with a higher risk of impaired quality of life [8], less optimal self-care [9], incident complications, and mortality [8,11]. However, to date there are few methodologically well-designed studies on the effectiveness of psychological interventions for people with diabetes and emotional complaints. In addition, the majority of these studies have focused on improving self-management instead of emotional well-being. Moreover, the few randomized studies that have examined the effectiveness of interventions in reducing emotional problems in people with diabetes often focused on depression. For this reason, this study is clearly of added value in the research field of diabetes and emotional problems, as we have taken a broader perspective and focused on emotional distress (depression, anxiety, and general distress).

The study design has a number of important strengths. First, the present study has more power to generate knowledge on the effectiveness of a mindfulness-based intervention for DM patients with emotional problems than former studies examining mindfulness in DM patients. As mentioned before, only two studies have been done on this subject, of which one lacked a control group and one did not include emotional well-being as an outcome [25,26]. Second, an additional strength of this study is the inclusion of both psychological and clinical measures, while most randomized controlled trials examining mindfulness interventions include psychological measures only. Finally, another strong aspect of this study is the examination of factors that potentially moderate the effectiveness of the mindfulness intervention, including clinical (e.g. complications) and psychological (e.g. personality) variables. Results may facilitate more effective allocation of patients to treatments.

The recruitment has already started in the Catharina Hospital in Eindhoven in spring 2010 and in the Maxima Medical Center in autumn 2010. At present, 969 individuals have been screened for emotional problems. Of those, 811 did not qualify: 658 had a score above 12 on the WHO-5 screening instrument, and 153 were ineligible (no mastery of the Dutch language, psychiatric disorder, or severe physical condition). Of the eligible patients, 120 declined participation (no perceived need or motivation for the training or an incompatible working schedule). At present, 42 patients are interested to participate, of whom 16 have been enrolled so far.

The recruitment of a sufficient number of patients will be a challenge. For instance, the mindfulness intervention requires participants to commit to attending eight two-hour group sessions and to practice exercises at home for five days per week. For people who have busy lives this sometimes is a challenge to comply with, which may make them decline participation or drop out of the study.

Concerning the benefits of the present study, the results will provide valuable information regarding the effectiveness of the mindfulness intervention for DM patients in improving emotional well-being. We will also gain insight in the pros and cons of a possible implementation of the intervention in usual medical care of DM patients. By doing this, we aim to find ways that can contribute to increased emotional well-being and quality of life in patients with diabetes mellitus.

In conclusion, considering the prospected increase of the prevalence of diabetes, the levels of emotional distress in this patient group, and the incompleteness of the current literature on effective psychological interventions for the distressed patients, well-designed trials on psychological interventions are a welcome addition in the diabetes research. In the present randomized controlled trial the effectiveness of a psychological intervention will be examined in which the cultivation of mindfulness (the direction of attention to one's experiences in the present moment in an open and accepting manner) plays a central role. This intervention may be an effective alternative to traditional cognitive behavioral therapy in improving emotional well-being in DM patients. The first results of the study will become available in 2012.
